### Fidelity

The providers of the intervention and control treatments will be trained in the delivery via a face-to-face training session and through provision of a handbook to standardise treatment delivery. Alongside the handbook, providers will have a catalogue of videos of the delivery of the treatments to aid delivery skills.

Providers will be observed by an external member of the study team to ensure adherence to treatment delivery, accommodate for provider differences and prevent provider drift. These observations will be made once every month during the first 3 months of the trial. They will then be observed once every 3 months for the rest of the trial. Providers will keep written records of treatment delivery to ensure delivery of the correct dose of treatment.

In order to ensure participant receipt and correct enactment of the treatments, participants will be shown each exercise, and then asked to describe and demonstrate the exercise back to the provider. Participants will also be asked to confirm how many ARC exercises they have been asked to undertake and will be provided with an exercise diary to document enactment of the exercises. The ARC exercise diary will be collected by the study team on the final outcome assessment visit. The outcome assessor will also be observed whilst conducting outcomes measures on three occasions across the duration of the study.

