#### Manuals

Participants will be provided with both paper- and web-based password-protected video-based training manuals on how to undertake the ARC treatment. Participants will also be given an exercise and falls diary.

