### Falls

Falls diaries will be given to each participant to complete. The providers (a research physiotherapist and a research associate) will check these weekly during face-to-face visits, and any falls between the 6 and 10-week outcome measures will be confirmed by the outcome assessor. Throughout the trial, the following definition of a fall will be applied: ‘A fall is described as an event in which the participant has lost their balance and landed on the floor or ground or lower level, including a slip or trip’ [44]. The falls diaries will be collected by the study team on the final outcome assessment visit.

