#### Recording and reporting of adverse events

This study will only report adverse events which are considered to be serious.

Serious adverse events *exclude*:
Pre-planned hospitalisationsScheduled treatment for pre-existing conditions.

The capture of potential SAEs will take place at the study outcome assessments by including the following questions in the outcome proforma: “are there any new medical problems since the last study assessment?” In addition, we will specifically enquire about falls in response to the participants falls diaries. For any events which fulfil the criteria to be a SAE and are unreported, the study SAE form will be completed.

Events considered to be SAEs will subsequently be documented onto a separate study SAE form, and a causality and expectedness assessment will be performed. As study investigators or other members of the research team may become aware of SAEs at times other than at outcome assessment appointments, the SAE form will also be used to directly capture these events.

Initial/provisional SAE reports can be made by telephone or email to the study co-ordinating centre. All initial/provisional reports must be followed by a fully completed SAE form. If incomplete information is available at the time of this initial report, further information must be provided on a follow-up form as soon as it is available. All SAEs regardless of causality or expectedness will be reported to the chief investigator and trial sponsor (Northumbria NHS Foundation Trust) in line with local policies. The main REC will be notified of related and unexpected SAEs within 15 days of the chief investigator becoming aware of the event.

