### Blinding

This study will be single blinded. Outcome assessments will be performed by researchers blinded to treatment allocation. After each assessment, the researcher will be asked to record whether they have unintentionally become aware of treatment allocation. Success of outcome assessment blinding will be reported. Emergency un-blinding will not be required for this study.

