### Data analysis

Objectives 1–3: Recruitment will be described as rate/month (total and per site). Adherence will be described using data from the exercise diaries (number of planned sessions completed). Acceptability and completeness of methods of data collection will be described using percentages from both treatments.

Objective 4: Retention will be described as percentage from both treatments.

Objective 5: The success of outcome measurement blinding will be described (%).

Objective 6: Adverse events pertaining to the study for each treatment will be described (number of events).

Objective 7: The views of study participants about undertaking the ARC treatment at home and in the community will be described. Summary statistics will be used for answers to closed questions and open questions will be thematically analysed.

Objective 8: The views of providers and clinical therapists about delivery of the study treatments will be described. Summary statistics will be used for answers to closed questions and open questions will be thematically analysed.

Objective 9: As this is a pilot study, statistical comparisons of clinical outcomes (e.g. dynamic gait index, see above) and accelerometer data between treatments will not be undertaken and data will be presented as summary descriptive statistics. To determine which outcome measures to take forwards to a main trial, we plan to review data completeness, patient/staff feedback about acceptability and any new emerging literature about most appropriate measures, to inform decisions. This review will also determine the most appropriate primary outcome measure. Data collected for this selected primary outcome measure (e.g. standard deviation) will subsequently be used as appropriate by statisticians to inform a power calculation for a definitive trial.

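### Collecting the ARC exercise diary at the blinded 10-week visit creates an avoidable unblinding risk and puts the record of self-managed sessions at risk

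*Protocol article*

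**What the plan says.** All references are to the protocol article.

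- **Fidelity:** "The ARC exercise diary will be collected by the study team on the final outcome assessment visit". Providers also keep written records of the treatment they deliver.
- **Falls:** "The falls diaries will be collected by the study team on the final outcome assessment visit". For the follow-up period, "any falls between the 6 and 10-week outcome measures will be confirmed by the outcome assessor".
- **Recording and reporting of adverse events:** at the outcome assessments, "In addition, we will specifically enquire about falls in response to the participants falls diaries".
- **Blinding:** "Outcome assessments will be performed by researchers blinded to treatment allocation". The only stated check comes after each assessment, when "the researcher will be asked to record whether they have unintentionally become aware of treatment allocation".
- **Manuals (ARC arm):** "Participants will also be given an exercise and falls diary". The matching paragraph for controls (Materials) lists an exercise diary and a falls diary as two items.
- **Data analysis, objectives 1–3:** "Adherence will be described using data from the exercise diaries (number of planned sessions completed". Study objectives and Progression criteria name two sources for adherence: provider observation and exercise diaries.

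**The concern.** Two separate aims meet at one visit. Falls have to be followed to week 10, so the assessor needs the falls information then. The exercise diary concerns a programme that finishes at week 6, yet it is held until the same visit and carries the name of the experimental treatment. If it is handed over in front of the assessor, allocation is revealed. Objective 5 would then partly measure an artefact of the trial's own logistics rather than whether blinding can work in a definitive trial.

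The second issue is loss of data. Adherence is primary objective 2 and one of three progression criteria. For the unsupervised sessions the diary is the only record named, and the only retrieval point stated is about four weeks after treatment ends. People who drift away in that interval may not be typical adherers, so the loss need not be random.

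**Working it through.** **Reproducing the plan's denominator.** Inputs: 60 participants (Sample size), and 18 sessions each, of which 12 are independent in both arms (the Dose and duration and Mode of delivery paragraphs).

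- Total: 60 × 18 = 1080, as printed in Progression criteria.
- Self-managed: 60 × 12 = 720, or 720/1080 = 66.7%.
- Remainder: 60 × 6 = 360. These are the sessions for which provider observation and provider records are available. Weekly control contact may be by telephone (control Mode of delivery), so direct observation could be thinner in that arm.

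**Sessions left without a record.** If k participants are not seen at week 10 and their diaries are not otherwise recovered, 12k planned sessions are undocumented. The protocol gives no attrition rate, so k is assumed:

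| Assumed not seen | k | 12k | 12k/1080 |
|---|---|---|---|
| 5% | 3 | 36 | 3.3% |
| 10% | 6 | 72 | 6.7% |
| 15% | 9 | 108 | 10.0% |
| 20% | 12 | 144 | 13.3% |

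**Effect on the adherence criterion.** The article states no rule for a missing diary, so two are illustrated.

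1. *Counted as zero, with true adherence 85% in everyone.* Apparent adherence = 0.85 × (1080 − 12k)/1080. For k = 3, 6, 9, 12 this is 82.2%, 79.3%, 76.5% and 73.7%. At k = 6 the count is 0.85 × 1008 = 856.8. The error is downward.
2. *Excluded, with self-managed adherence of 40% in those not seen and 82% for all other sessions (both assumed).* For k = 6, the true figure is [54 × 18 × 0.82 + 6 × (6 × 0.82 + 12 × 0.40)]/1080 = (797.04 + 58.32)/1080 = 79.2%. The observed figure is (797.04 + 29.52)/1008 = 82.0%. The error is upward.

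In both cases the result at k = 6 lands on the wrong side of the 80% green line. The protocol prints 840 beside that 80%, whereas 0.80 × 1080 = 864 and 840/1080 = 77.8%. Against 840, the k = 6 examples would not change colour. Of the tabulated values, the first rule would cross at k = 9 (826.2 sessions). The second would cross at k = 12, where true adherence is [48 × 18 × 0.82 + 12 × 9.72]/1080 = 76.4%.

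**Blinding.** No arithmetic applies. Fidelity and Falls place both diaries at the last assessment visit; Blinding says the assessment is done by blinded staff; Falls and the adverse event section give the assessor a task that uses falls information. No neutral label, sealed return or order of tasks is stated. The self-report in Blinding detects unblinding afterwards and does not prevent it.

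**The case against.** Much can fairly be said for the plan.

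- **Who collects.** A reader might infer that the assessor takes the diary and is therefore unblinded. The text says the study team collects it, and Fidelity mentions the outcome assessor separately. Only a risk is supported.
- **One booklet or two.** The ARC Manuals wording might be read as a single combined booklet, which would force the assessor to handle the exercise record. Falls says every participant receives a falls diary and gives it its own collection sentence, so two documents are at least as likely. If it were one booklet, keeping it to week 10 would have a reason.
- **Bias in outcomes.** A reader might infer that a treatment comparison is distorted. Data analysis (objective 9) rules out between-arm comparison of clinical outcomes. The 6-week ratings are unaffected, and the week-10 tests are affected only if the diary is seen first, which the text does not say.
- **Sole source of adherence.** The sentence in Data analysis might be read as making the diary the only source. It does not say so, and Study objectives, Progression criteria and Fidelity all bring in provider observation or records.
- **Recoverability.** Nothing forbids postal return, which is already used for accelerometers. Those who stop treatment are asked whether they will still attend assessments.

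These points limit the finding but do not remove it. The handover is still fixed at a blinded visit without a stated safeguard, and no other retrieval route is given for the exercise diary. Providers check falls diaries weekly, but nothing says that exercise entries are copied.

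**Conclusion.** The point holds as a design weakness worth correcting. An allocation-revealing document is scheduled for collection at a blinded visit when it could be collected four weeks sooner. This is an avoidable risk to objective 5; the documents do not show that unblinding will occur.

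For primary objective 2, the exposure is limited to the 720 self-managed sessions. With an assumed 5% to 20% not seen at week 10, 36 to 144 planned sessions (3.3% to 13.3% of 1080) would lack a record. That range assumes no other recovery of diaries. It counts planned sessions without a record, which is not the same as the error in the adherence percentage. The error may run either way, depending on how missing diaries are handled and how well those participants adhered. That people not seen adhere less well is an assumption; the protocol does not report it.

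**What to change.** 1. In both arms, have the unblinded treatment provider collect the exercise diary at the last treatment contact. Otherwise, have it returned in a pre-paid envelope at week 6 or when a participant stops treatment.
2. Issue a separate falls diary with identical labelling in both arms, kept to week 10, and have the assessor review it only after the performance tests are finished.
3. In Data analysis, state that adherence uses provider records for supervised sessions and diaries for self-managed ones, in line with Study objectives and Progression criteria.

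The cost is a wording change, some relabelling and envelopes. The drawback is that some posted diaries may not come back, so collection by the provider in person is preferable where possible. Trial status reports 16 of 60 recruited at submission, so at that time 60 − 16 = 44 participants were still to be recruited and could be covered in full.

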### Study data collection

All study data will be entered locally by the study team onto a secure online database (MACRO) maintained by Newcastle Clinical Trials Unit. Pseudo-anonymised participant identification codes will be used. Study paper CRF’s will be kept securely in the local investigator site file.

### Blinding

This study will be single blinded. Outcome assessments will be performed by researchers blinded to treatment allocation. After each assessment, the researcher will be asked to record whether they have unintentionally become aware of treatment allocation. Success of outcome assessment blinding will be reported. Emergency un-blinding will not be required for this study.

### Data analysis

Objectives 1–3: Recruitment will be described as rate/month (total and per site). Adherence will be described using data from the exercise diaries (number of planned sessions completed). Acceptability and completeness of methods of data collection will be described using percentages from both treatments.

Objective 4: Retention will be described as percentage from both treatments.

Objective 5: The success of outcome measurement blinding will be described (%).

Objective 6: Adverse events pertaining to the study for each treatment will be described (number of events).

Objective 7: The views of study participants about undertaking the ARC treatment at home and in the community will be described. Summary statistics will be used for answers to closed questions and open questions will be thematically analysed.

Objective 8: The views of providers and clinical therapists about delivery of the study treatments will be described. Summary statistics will be used for answers to closed questions and open questions will be thematically analysed.

Objective 9: As this is a pilot study, statistical comparisons of clinical outcomes (e.g. dynamic gait index, see above) and accelerometer data between treatments will not be undertaken and data will be presented as summary descriptive statistics. To determine which outcome measures to take forwards to a main trial, we plan to review data completeness, patient/staff feedback about acceptability and any new emerging literature about most appropriate measures, to inform decisions. This review will also determine the most appropriate primary outcome measure. Data collected for this selected primary outcome measure (e.g. standard deviation) will subsequently be used as appropriate by statisticians to inform a power calculation for a definitive trial.

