### Study objectives

Primary objectives:
To identify monthly recruitment rates to determine whether it is possible to enrol at least one patient per month from each study centre.To report participant adherence to ARC intervention and control treatment arms (provider observation and exercise diaries).To assess the acceptability and completeness of proposed methods of data collection to ensure they are feasible for a definitive trial.

Secondary objectives:
4.To report participant retention to the study.5.To report the success of outcome assessor blinding to participant treatment allocation.6.To report adverse events in control and intervention treatments during the study.7.To report the views of study participants about undertaking the ARC intervention at home and in the community.8.To report the views of providers and clinical therapists about the study protocol.9.To gather data to allow reporting of summary statistics to allow estimation of the sample size requirements for the definitive trial.

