### Progression criteria

Progression criteria have been set based upon recruitment, treatment adherence and data completeness to determine whether progression to a definitive trial is appropriate. These criteria and the traffic light system applied are based upon recommendations from Avery et al. [20].

Potential success criteria:
*Recruitment of participants*: green = an average of at least four patients per month recruited across the four sites; amber = an average of at least three patients per month recruited across the four sites; red = two or fewer patients recruited per month across the four sites.*Treatment adherence*: green = an average of at least 80% (840 out of 1080) supervised and self-monitored treatment sessions completed across the intervention and control treatment cohorts measured by provider observation and exercise diaries; amber = an average of at least 70% (756 out of 1080) supervised and self-monitored treatment sessions completed by participants; red = an average of 70% or less supervised and self-monitored treatment sessions completed by participants.*Data completeness:* green = completion (no missing data) of over 85% of key outcome measures (7 day accelerometer measurement; walking speed in the home; miniBEST and self-completion questionnaires: for full description see the ’Baseline assessment’ section) at 10-week outcome assessment for all those completing the treatment programmes; amber = completion of over 70% of key outcome measures at 10 weeks; red = completion of 70% or less of key outcome measures at 10 weeks.

Whilst these criteria will be used to evaluate the likely feasibility of a larger trial, they will primarily be employed to optimise the study design and identify/address issues in order to take remedial steps in a timely fashion. An example of this would be problems around recruitment.

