### Sample size

We aim to recruit 60 participants in 15 months at a rate of one patient per trial centre per month. This sample size has been selected as it is the sample recommended for pilot studies [21]. We believe that this is a realistic recruitment rate informed by previous trials [22, 23].

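### The analysis section takes adherence from exercise diaries and names no other source, while Objective 2 and the progression criterion define it by provider observation plus diaries

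*Protocol article*

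**What the plan says.** Three places in the protocol article say how adherence is measured.

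- Study objectives, Objective 2 (a primary objective): "To report participant adherence to ARC intervention and control treatment arms (provider observation and exercise diaries".
- Progression criteria, treatment adherence: the count is of "supervised and self-monitored treatment sessions completed across the intervention and control treatment cohorts measured by provider observation and exercise diaries". Green is "an average of at least 80% (840 out of 1080" and amber is "an average of at least 70% (756 out of 1080".
- Data analysis, Objectives 1–3: "Adherence will be described using data from the exercise diaries (number of planned sessions completed".

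Two further places bear on it. Under Fidelity, "Providers will keep written records of treatment delivery to ensure delivery of the correct dose of treatment". The same section has the ARC exercise diary collected once, at the final outcome visit. The Mode of delivery sections give each ARC participant six supervised sessions out of 18. Control participants get a weekly provider contact, which may be a visit or a telephone call.

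**The concern.** The objective and the criterion use two sources, and the sentence that says how the objective will be analysed uses one. The source it omits does not depend on the participant: providers are already required to record what they deliver. The source it keeps is a self-completed document handed in four weeks after the six-week programme ends, at a visit that a participant who withdraws may never reach.

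Adherence is one of three progression criteria. If the diary is the sole source, a lost diary either erases sessions the provider saw completed or removes that participant from the calculation. In the second case the figure describes only those who returned a diary, and it is probably too high if non-return goes with poor adherence. In either case it is not the quantity for which the 80% and 70% lines were set.

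**Working it through.** **The plan's own figures.** Sample size: "We aim to recruit 60 participants in 15 months". With 18 planned sessions each, 60 × 18 = 1080, which matches the printed denominator. Amber: 0.70 × 1080 = 756, which matches. Green: 0.80 × 1080 = 864, but the protocol prints 840, and 840/1080 = 77.8%. That mismatch is a separate matter, but it affects how any colour is read, so both green lines are used below. A count of 756 or more is taken as amber.

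**How much the provider record covers.** With records in both arms: 6 × 60 = 360 of 1080 (33.3%). With records in the ARC arm only, at 30 participants: 6 × 30 = 180 of 1080 (16.7%).

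**Formulas.** Let k be the number of lost diaries and s the self-managed sessions done out of 12. Assume all 6 weekly sessions are done, a lost diary counts as not done, and the denominator stays at 1080.

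- Diaries alone: (60 − k)(6 + s)
- Both sources, provider records in both arms: (60 − k)(6 + s) + 6k
- Both sources, provider records in the ARC arm only, losses split evenly: (60 − k)(6 + s) + 3k

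Neither k nor s is given in the protocol, so every value of them here is an assumption.

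**Worked case, s = 10** (full-data adherence 60 × 16 = 960, or 88.9%):

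- k = 8, diaries alone: 52 × 16 = 832 (77.0%), amber at either line.
- k = 8, both sources in both arms: 832 + 48 = 880 (81.5%), green at either line.
- k = 8, provider records in the ARC arm only: 832 + 24 = 856 (79.3%), green at 840 but amber at 864.
- k = 13: 47 × 16 = 752 (69.6%, red) from diaries alone, against 752 + 78 = 830 (76.9%, amber) from both sources in both arms.

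**Range.** Number of lost diaries at which the count first falls below each line (diaries alone / both sources in both arms):

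| s of 12 | below 864 | below 840 | below 756 |
|---|---|---|---|
| 9 | 3 / 5 | 5 / 7 | 10 / 17 |
| 10 | 7 / 10 | 8 / 13 | 13 / 21 |
| 11 | 10 / 15 | 11 / 17 | 16 / 25 |
| 12 | 13 / 19 | 14 / 21 | 19 / 28 |

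The two measures give different colours only between the paired numbers. At s = 10 they differ between green and amber for 7–9 lost diaries at the 864 line and for 8–12 at the 840 line. The combined count also falls, by s sessions per lost diary instead of 6 + s.

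**The case against.** The strongest reply is that the analysis sentence is a one-line summary in a condensed article. It does not say that diaries are the *only* source, and it does not restate the progression criterion, which is defined with both sources elsewhere. On that reading the sentence is incomplete shorthand and the criterion governs. The protocol also says the criteria serve mainly to improve the design and to catch problems in time, so a shifted colour is not a strict stop.

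Part of this stands. Nothing shows a decision to discard provider records, and a reader who infers one goes further than the text. But the sentence is not silent: it names a source, and that source differs from the one in Objective 2 and in the criterion. Nothing says which passage prevails.

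A reader might also infer that a handful of lost diaries is enough to change the colour. The documents do not support that as a general statement. Take 95% completion of supervised and 80% of self-managed sessions: 6 × 0.95 + 12 × 0.80 = 15.3 sessions per person. With five lost diaries, diaries alone give 55 × 15.3 = 841.5 (77.9%), which is still green at the printed 840. At 864 it is amber, against 841.5 + 5 × 5.7 = 870 (80.6%, green) if providers' records cover both arms. If they cover the ARC arm only and losses split evenly, the combined count averages 841.5 + 14.25 = 855.75 (79.2%), amber on both measures.

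Finally, a sensitivity figure restricted to returned diaries and tables by source and arm are analysis-plan detail. An article may leave them out, and their absence is not part of this point.

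**Conclusion.** The inconsistency is real and is stated in the text: one primary objective has two definitions of its data source, and the analysis sentence does not match the criterion it feeds. Followed literally, it drops an existing record of up to a third of all planned sessions, or about a sixth if only ARC sessions are observed.

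The effect on the colour is conditional. It needs lost diaries counted as not done against a fixed 1080, and losses within a particular range. Eight lost of 60 (13%) suffices at either green line under the worked assumptions with provider records in both arms. With records in the ARC arm only, the change appears at 840 but not at 864. Below those losses the colour may not move. This is a low-cost correction that should be made, not evidence that the adherence result will be wrong.

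**What to change.** Amend the Objectives 1–3 sentence under Data analysis so that it agrees with Objective 2 and the progression criterion:

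- count supervised sessions from the providers' written records;
- count self-managed sessions from the exercise diaries;
- take control-arm weeks handled by telephone from the diary, since no provider observed a session;
- divide by 18 sessions per randomised participant, which is how the protocol reaches 1080.

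The cost is one sentence. The Fidelity section already requires the provider records, so no new data are collected. Trial status reports 16 of 60 participants recruited when the article was submitted, so at that stage the wording could be settled before the adherence result was known. Because 12 of 18 sessions are unsupervised, the combined figure will still fall when diaries are lost, so the change limits the problem without removing it. The green line's printed count and percentage (840 against 864) should be reconciled in the same revision, since the colour cannot be read unambiguously until they are.

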### Randomisation

Sealed envelope centralised computer-based randomisation service (https://www.sealedenvelope.com/) will be used for randomisation. Allocation concealment will be ensured, as the randomisation code will not be allocated until after the participant has been consented into the trial. Randomisation will take place after all baseline outcome measures have been completed. Once baseline assessments have been completed by the assessors, the providers of the study treatments will use the sealed envelope randomisation service to randomise participants 1:1 into either the ARC intervention or control treatments. Simple randomisations will be used. The randomisation service will be used to number participants.

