### Safety

The safety of the intervention will be evaluated by examining the occurrence of adverse events and falls.

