#### Adverse event

Any untoward medical occurrence in a subject to whom a study intervention or procedure has been administered, including occurrences which are not necessarily caused by or related to that intervention. An adverse event (AE), therefore, does not necessarily have a causal relationship with the treatment. In this context, ‘treatment’ includes all interventions (including comparative agents) administered during the course of the study. Medical conditions/diseases present before starting study treatment are only considered adverse events if they worsen after starting study treatment.

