#### Related AE

Related AE is an AE that results from administration of any of the research study procedures. All AEs judged by either the reporting investigator or the sponsor as having reasonable causal relationship to a study procedure qualify as ‘related adverse events’. The expression “reasonable causal relationship” means to convey in general that there is evidence or argument to suggest a causal relationship.

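### Objective 6 fixes the adverse event summary as a bare event count per treatment, with no participants affected, no denominator, an undefined scope and no summary for falls

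*Protocol article*

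**What the plan says.** - Study objectives, Objective 6: "To report adverse events in control and intervention treatments during the study". No limit by causality is set.
- Safety: "The safety of the intervention will be evaluated by examining the occurrence of adverse events and falls". Falls have their own diary and definition in the Falls section.
- Data analysis, Objective 6: "Adverse events pertaining to the study for each treatment will be described (number of events". In the same section recruitment is a monthly rate, and retention and blinding are percentages. Adverse events get a number only, and falls are not mentioned.
- Randomisation: "Simple randomisations will be used". The ratio is 1:1 (Study design), with nothing to force equal arm sizes.
- Recording and reporting of adverse events: "This study will only report adverse events which are considered to be serious". Also: "All SAEs regardless of causality or expectedness will be reported to the chief investigator and trial sponsor".
- The definition of an adverse event covers occurrences "including occurrences which are not necessarily caused by or related to that intervention". A separate term exists for events "having reasonable causal relationship to a study procedure qualify as ‘related adverse events". The Objective 6 analysis sentence uses neither term.

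**The concern.** Three features of one sentence weaken the safety description.

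1. **No participants and no denominator.** A count by arm can be read properly only beside the number at risk and the number of people who contributed events. Several events in one person and single events in several people give the same count.
2. **Undefined scope.** The article defines adverse events and related adverse events, then analyses a third, undefined category. Two analysts could build different tables from it.
3. **No summary for falls.** Falls are one of the two named safety components, yet the Data analysis section gives them none.

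Between-arm tests of clinical outcomes are ruled out, so readers will compare the described numbers directly, and their form matters for that reason. What is at stake is how interpretable a named secondary objective will be.

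**Working it through.** **Sample size.** Inputs: 4 centres (Study setting), and 1 participant per centre per month for 15 months (Sample size). 4 × 1 × 15 = 60, which reproduces the stated target.

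**Arm sizes under simple 1:1 randomisation.** The size of one arm is Binomial(60, 0.5). The chance of a split of (30 − d):(30 + d) or worse, in either direction, is 2 × P(X ≤ 30 − d). At equal risk per person, the expected ratio of event counts at exactly that split is (30 + d)/(30 − d).

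| Split | Chance of this split or worse | Expected count ratio at this split |
|---|---|---|
| 26:34 | 36.6% | 34/26 = 1.31 |
| 25:35 | 24.5% | 35/25 = 1.40 |
| 24:36 | 15.5% | 36/24 = 1.50 |
| 22:38 | 5.2% | 38/22 = 1.73 |

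An exact 30:30 split has a chance of 10.3%. The article gives no event rates. If 0.3 events per person is assumed in both arms, a 25:35 split gives 25 × 0.3 = 7.5 against 35 × 0.3 = 10.5 expected events. The counts differ although the rate per person is the same.

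**Repeat events (assumed example).** Suppose 5 of 30 participants in each arm have an event, and one of them has 6. The counts are 4 + 6 = 10 against 5, a ratio of 2.0. The participants affected are 5/30 against 5/30, or 17% in each arm. This applies to any count in which one person can contribute more than once. It applies to non-serious falls only if falls are tallied as events in the count, which the article does not say.

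**What counting participants would change.** Null simulations were run with 30 per arm and no true difference, recording how often one arm's figure is at least double the other's. All rates are assumed.

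- Clustered events (negative binomial, mean 0.3 to 0.5 per person, dispersion 0.2 to 0.5): 22% to 42% of trials for event counts, against 13% to 32% for participants with at least one event.
- Sparse events (Poisson, 0.03 to 0.1 per person): 53% to 68% for counts, against 52% to 67% for participants.

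The participant figure helps where events cluster within people. It makes almost no difference where events are rare.

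**Scope, side by side.** The objective sets no causality limit, the adverse event definition includes unrelated occurrences, and all serious events go to the chief investigator and sponsor whatever their cause. Only the analysis sentence adds a qualifier, and it is not the defined term for related events.

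**The case against.** - **Reporting is limited to serious events, and falls are handled separately.** This stands. A reader might infer that one repeat faller will distort the Objective 6 count. The article does not support that: a fall that is not serious need not enter the count at all. What remains is that falls have no stated summary of their own.
- **The qualifier may simply mean occurring in the study.** This also stands. A reader might infer that events judged unrelated will drop out. That is one possible reading of an undefined phrase, and the rest of the article sets no causality limit. The defect is ambiguity; no exclusion is shown.
- **Arm sizes will be visible elsewhere.** True, because retention as a percentage by treatment needs them. A reader could divide the counts by hand, but could not recover how many people had an event.
- **Participant counts are ordinary table-shell detail, and this is a condensed article.** A fuller analysis plan may well add them. But the article states the metric for this objective, so the point is about a stated choice.
- **Unequal observation time.** Assessments are fixed at 6 and 10 weeks for everyone, so exposure differs only through withdrawal or dropout. A summary per unit of person-time is not essential.
- **Nothing turns on the count.** Adverse events are not among the progression criteria and the study is descriptive. This limits the consequence to interpretability.

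**Conclusion.** The point holds in a limited form. The Objective 6 sentence fixes a raw event count by treatment, leaves its scope undefined and gives falls no summary. Simple randomisation makes the missing denominator more than a formality: 25:35 or worse in 24.5% of trials, and a 1.4-fold expected count ratio at 25:35 with equal risk. These two figures rest only on 60 participants and simple 1:1 allocation. The event-rate examples and the simulated ranges rest on assumed rates and clustering.

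The result is a less interpretable safety description. A reader might go further and infer a wrong safety or progression decision; the article ties neither to this count. Nor would the better summary settle chance differences: under the assumed clustered rates, a two-fold gap still appears in 13% to 32% of null trials.

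**What to change.** Replace the Objective 6 analysis sentence with:

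> *Every serious adverse event captured under the Recording and reporting of adverse events section, regardless of causality, and separately every diary-recorded fall, will be described by treatment as the number of events and as the number and percentage of randomised participants with at least one event. Related events will be shown as a subset.*

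This removes the undefined qualifier, matches the serious-only reporting rule and gives falls a summary. It costs one sentence and one further table from data already being collected, with no extra participants, visits or forms.
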